**Methods/Design:**

A short PTSD-screener assesses the possible presence of PTSD in adult patients (21- to 65- years old) with psychotic disorders, while the Clinician Administered PTSD Scale interview will be used for the diagnosis of current PTSD. The M.I.N.I. Plus interview will be used for diagnosing lifetime psychotic disorders and mood disorders with psychotic features. The purpose is to include consenting participants (N = 240) in a multi-site single blind randomized clinical trial. Patients will be allocated to one of three treatment conditions (N = 80 each): prolonged exposure or EMDR (both consisting of eight weekly sessions of 90 minutes each) or a six-month waiting list. All participants are subjected to blind assessments at pre-treatment, twomonths post treatment, and six monthspost treatment. In addition, participants in the experimental conditions will have assessments at mid treatment and at 12 months follow-up.

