**Discussion:**

The results from the post treatment measurement can be considered strong empirical indicators of the safety and effectiveness of prolonged exposure and EMDR. The six-month and twelve-month follow-up data have the potential of reliably providing documentation of the long-term effects of both treatments on the various outcome variables. Data from pre-treatment and midtreatment can be used to reveal possible pathways of change.

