## Objectives

### Primary objective –effects of treatment on PTSD symptoms and safety

In a sample of patients who receive treatment as usual (TAU) for a current diagnosis of psychosis this study examines: a) the efficacy of PE versus waiting list, and of EMDR versus waiting list, on the symptomatology of a comorbid PTSD; and b) the safety of PE versus waiting list and EMDR versus waiting list in the treatment of PTSD.

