## Methods/Design

### Design

The T.TIP study is a single blind randomized controlled trial with three arms: PE, EMDR and a waiting list. The three groups are compared at pre-treatment (T0), at post treatment at two months (T2) and at six months (T6), on a set of variables that are linked to the various research questions. Mediator and moderator variables are assessed again at midtreatment (T1). A 12-month treatment intervention follow-up measurement (T12) will give indications whether treatment effects endure. The waiting list condition will receive the treatment of choice after sixmonths (T6).

The assessing research assistants are blind to the participants’ research condition.

The design of this study was approved by the Medical Ethics Committee of the medical centre of the VU University and is registered as N:36649.029.12.

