### Measurements

Subjects participate in the study for 12 months. At T0, the RA assesses baseline measurements of all primary, secondary, tertiary and quaternary variables. At T1, at midtreatment, participants in treatment conditions are assessed for their scores on the moderator and mediator variables by self-report questionnaires handed out by the therapist. At T2, the end of treatment, the RA assesses treatment outcome variables. T6 is the first follow-up measurement, and this is the starting point for treatment for the waiting list group. T12 is the 12-month follow up measurement for the PE and EMDR group.

For participants in the treatment conditions PE and EMDR some assessments are planned within sessions: PTSD symptom severity, therapy burden, harm expectancy (pre-session) and experienced harm (post-session), adverse events (pre- and post-session), credibility of treatment and memory characteristics. Note that therapists are also assessed independently from the participants for perceived and experienced treatment burden credibility and harm, before, during and after treatment.

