The T.TIP Adverse Events Questionnaire (T-AEQ) is a checklist that establishes treatment safety. In seven questions the patient is asked to report any self-inflicted pain or injury, suicide attempt, deliberately hurting or physically wounding another person, excessive use of alcohol, excessive use of drugs, having needed help because of a crisis and being admitted to a psychiatric hospital. The time frame is two months.

The Adverse Events session ratings assesses adverse events in the participant before and after treatment sessions (sessions two and three), for example, being suicidal, hearing voices. Participants respond on a 10-point visual analog scale (VAS;‘no, not at all’ to ‘yes, very much’) to the questions.

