### Measurements – effects of treatment on psychopathology and cost effectiveness

See Table 2, Secondary outcome measurements.

**Table 1 T1:** Measurements primary objectives: PTSD and safety of treatment

**Primary outcome**	**MeasurementInterview(i)**, **self-report(s)**	**T0 baseline**	**T1 midtreatment**	**Within-session (1–8)**	**T2 posttreatment**	**T6 FU 6 months**	**T12 FU 12 months**
PTSD	CAPS (i)	x			x	x	x
	PSS-SR (s)	x		1, 2, 3, 4, 5, 6, 7, 8	x	x	x
Adverse events	TAEQ (s)	x	x		x	x	x
	AE session ratings (s)			2 ,3			

*AE* adverse events, *CAPS* Clinician Administered Post traumatic stress disorder Scale, *FU* follow up, *PSS-SR* Posttraumatic Stress Disorder Symptom Scale - Self Report, *TAEQ* T.TIP Adverse Events Questionnaire.

**Table 2 T2:** Measurements secondary objectives: psychopathology and cost effectiveness

**Secondary outcome**	**MeasurementInterview(i),self-report(s)**	**T0 baseline**	**T1 midtreatment**	**T2 posttreatment**	**T6 FU 6 month**	**T12 FU 12 months**
Paranoid thinking	GPTS (s)	x		x	x	x
Verbal hallucinations	AHRS (i)	x		x	x	x
Delusions	DRS (i)	x		x	x	x
Basic assumptions	AVH-BAS (s)	x	x	x	x	x
Verbal hallucinations	ESM (s, psymate)	x		x		
Depression	BDI-II (s)	x		x	x	x
Social functioning	PSP (i)	x		x	x	x
Posttrauma cognitions	PTCI (s)	x	x	x	x	x
Remission	SCI-SR (i)	x		x	x	x
Care consumption	TiC-P (s)	x		x	x	x
Health outcome	EQ-5D (s)	x		x	x	x

*AHRS* Auditory Hallucination Rating Scale, *AVH-BAS* Auditory Verbal Hallucinations – Basic Assumptions Scale, *BDI-II* Beck Depression Inventory - II, *DRS* Delusion Rating Scale, *ESM* Experience Sampling Method, *EQ-5D™* EuroQol - 5 dimensions *GPTS* Green ParanoiaThought Scale, *PSP* Social Performance Scale *PTCI* Posttraumatic Cognitions Inventory, *SCI-SR* Structured Clinical Interview for Symptoms of Remission for the PANSS, *TiC-P* Trimbos/iMTA questionnaire for Costs associated with Psychiatric Illness - short version.

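### The safety checklist looks back two months but is given at months 2, 6 and 12, so it never asks about months 2–4 in any arm or months 6–10 in the treated arms.

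*Protocol article*

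**What the plan says.** The primary objective has two parts, and the second is "the safety of PE versus waiting list and EMDR versus waiting list in the treatment of PTSD". Under the measurements for PTSD symptoms and safety, the article says of the T-AEQ that it "is a checklist that establishes treatment safety". The form has seven self-report questions on self-injury, suicide attempt, harm to others, excessive alcohol, excessive drugs, crisis help and psychiatric admission. One look-back is given for all occasions: "The time frame is two months".

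Table 1, headed "Measurements primary objectives: PTSD and safety of treatment", marks the T-AEQ at T0, T1, T2, T6 and T12. The Design section places T2 at two months and T6 at six. The Measurements section identifies T2 with the end of the treatment course: "At T2, the end of treatment, the RA assesses treatment outcome variables". The waiting list is offered treatment after T6. According to the abstract, only "participants in the experimental conditions will have assessments at mid treatment and at 12 months follow-up", so T1 and T12 have no waiting-list counterpart. No other look-back is stated for T6 or T12.

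**The concern.** The look-back matches the spacing of visits only up to T2. After that the visits are four and then six months apart, while the question still reaches back two months. An event in an unasked month does not enter the measure on which the safety objective rests, and no later analysis can recover it.

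The first gap opens where treatment stops. The Background explains that clinicians fear crisis, admission, self-harm and suicidal behaviour after trauma treatment in these patients. A statement about safety over six months would have to cover the two months after the last session, and the T-AEQ as worded does not.

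**Working it through.** **Inputs.** Look-back of 2 months (T-AEQ description). Visits at months 0, 2, 6 and 12 (Design, Measurements and Table 1), with month 12 for PE and EMDR only. T1 taken at about month 1, an assumption (midpoint of eight weekly sessions). Months are counted from T0, visits are assumed to be on time, and patients are assumed to answer for exactly two months.

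**Method.** A form given at month *v* covers months *v* − 2 to *v*. Between consecutive visits at *a* and *b*, the unasked time is (*b* − *a*) − 2 where that is positive, and its share is ((*b* − *a*) − 2)/(*b* − *a*). The article states no coverage figure, so there is none to reproduce.

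| Interval | Arms | Months asked about | Months not asked about | Share missed |
|---|---|---|---|---|
| T0–T2 | all three | 0–2 | none | 0/2 = 0% |
| T2–T6 | all three | 4–6 | 2–4 | (4 − 2)/4 = 2/4 = 50% |
| T6–T12 | PE, EMDR | 10–12 | 6–10 | (6 − 2)/6 = 4/6 = 67% |
| T0–T6 | all three | 0–2, 4–6 | 2–4 | 2/6 = 33% |
| T0–T12 | PE, EMDR | 0–2, 4–6, 10–12 | 2–4, 6–10 | (2 + 4)/12 = 50% |

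**Does T1 help?** At about month 1 its window runs from month −1 to month 1. That lies inside the T0 and T2 windows, so it adds no time that is otherwise uncovered.

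**Does another listed instrument fill the gap?** The adverse-event session ratings are taken at sessions two and three, so only in treated patients and before T2. The TiC-P is given at T2, T6 and T12 and counts hospital stay, but it is a cost questionnaire with no stated look-back, and its described content does not include self-harm, suicide attempts or violence. Apart from hospital stay, nothing shown records these events for the missing months.

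**Sensitivity to visit timing.** The abstract could be read as placing T2 two months after the end of treatment. The Measurements section and the six-month waiting period speak against that. If it were so, and T6 and T12 moved with it, T2–T6 would still be four months and T6–T12 six. The 50% and 67% would stand, but T0–T2 would no longer be fully covered.

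**After the change below.** If the T6 form covers 4 months and the T12 form covers 6, unasked time falls to 0 of 4 and 0 of 6.

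**The case against.** A fixed two-month window is a defensible choice. It makes T0, T2 and T6 like for like and limits recall error in patients with psychosis. Asking since the last visit gives windows of unequal length and cannot be applied at T0. This stands, and it is why the fix keeps a two-month marker beside the longer question.

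Serious-adverse-event reporting may also exist in the full protocol, which is not shown. This stands too. The finding is about what the T-AEQ asks, and it does not show that such events go unrecorded in the trial altogether.

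Some stronger readings are tempting, and the article does not support them:

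- *The extra T1 form biases the comparison.* A reader might infer that treated patients get one more chance to report. But the Design section compares the three groups at T0, T2 and T6, and the Measurements section presents T1 as a mediator and moderator assessment. Nothing says that T1 reports enter a between-arm count.
- *The between-arm safety count is invalid.* Months 2–4 are missed alike in every arm. That loses events but does not by itself tilt the contrast. T2 and T6 each give a fair comparison for their own two months.
- *The T6–T12 gap weakens the primary safety objective.* That objective is set against the waiting list, which has no T12 assessment. The gap affects only uncontrolled follow-up.
- *The abstract's safety claim is undermined.* The article says that results from the post-treatment measurement "can be considered strong empirical indicators of the safety and effectiveness of prolonged exposure and EMDR". That refers to T2, where coverage is complete and equal.
- *The trial is too small to show safety.* This needs an event rate that the article does not give, and it contradicts no figure in the article.

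**Conclusion.** The point holds as one of completeness. The T-AEQ, as worded and scheduled, leaves 2 of the 6 randomised months unasked in all three arms, and 4 of the 6 months after T6 unasked in PE and EMDR. The first gap matters more, because it falls directly after treatment and within the randomised comparison. The size follows from the article's own look-back and visit months. It assumes visits on schedule and the same look-back at every visit, since no other is stated.

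The six-month safety comparison is incomplete, not biased, and the comparison at T2 is unaffected. This is a cheap improvement, not a flaw that overturns the design.

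**What to change.** 1. At T6 and T12, word the T-AEQ as 'since your last assessment (date)', with the date filled in by the research assistant.
2. On the same forms, have the patient mark which reported events fell in the last two months, so that the like-for-like comparison with T0 and T2 is kept.
3. By arm, report the number of patients with at least one event from T0 to T6, taken from the T2 and T6 forms, with the risk difference of each treatment against the waiting list and its 95% confidence interval.
4. Keep the T1 form as description within the treated arms, in line with the comparison points in the Design section.

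**Cost.** No new visit or instrument: a changed line on a seven-item checklist, one extra tick per item and one sentence in the analysis. The downside is poorer recall over four months at T6 and six at T12, and windows of unequal length, which the two-month tick offsets. The article says that recruitment is under way, so some early participants may complete T6 on the present wording. Their months 2–4 may be hard to recover, and the form version used should be recorded.

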### Measurements – effects of treatment on psychopathology and cost effectiveness

See Table 2, Secondary outcome measurements.

**Table 1 T1:** Measurements primary objectives: PTSD and safety of treatment

**Primary outcome**	**MeasurementInterview(i)**, **self-report(s)**	**T0 baseline**	**T1 midtreatment**	**Within-session (1–8)**	**T2 posttreatment**	**T6 FU 6 months**	**T12 FU 12 months**
PTSD	CAPS (i)	x			x	x	x
	PSS-SR (s)	x		1, 2, 3, 4, 5, 6, 7, 8	x	x	x
Adverse events	TAEQ (s)	x	x		x	x	x
	AE session ratings (s)			2 ,3			

*AE* adverse events, *CAPS* Clinician Administered Post traumatic stress disorder Scale, *FU* follow up, *PSS-SR* Posttraumatic Stress Disorder Symptom Scale - Self Report, *TAEQ* T.TIP Adverse Events Questionnaire.

**Table 2 T2:** Measurements secondary objectives: psychopathology and cost effectiveness

**Secondary outcome**	**MeasurementInterview(i),self-report(s)**	**T0 baseline**	**T1 midtreatment**	**T2 posttreatment**	**T6 FU 6 month**	**T12 FU 12 months**
Paranoid thinking	GPTS (s)	x		x	x	x
Verbal hallucinations	AHRS (i)	x		x	x	x
Delusions	DRS (i)	x		x	x	x
Basic assumptions	AVH-BAS (s)	x	x	x	x	x
Verbal hallucinations	ESM (s, psymate)	x		x		
Depression	BDI-II (s)	x		x	x	x
Social functioning	PSP (i)	x		x	x	x
Posttrauma cognitions	PTCI (s)	x	x	x	x	x
Remission	SCI-SR (i)	x		x	x	x
Care consumption	TiC-P (s)	x		x	x	x
Health outcome	EQ-5D (s)	x		x	x	x

*AHRS* Auditory Hallucination Rating Scale, *AVH-BAS* Auditory Verbal Hallucinations – Basic Assumptions Scale, *BDI-II* Beck Depression Inventory - II, *DRS* Delusion Rating Scale, *ESM* Experience Sampling Method, *EQ-5D™* EuroQol - 5 dimensions *GPTS* Green ParanoiaThought Scale, *PSP* Social Performance Scale *PTCI* Posttraumatic Cognitions Inventory, *SCI-SR* Structured Clinical Interview for Symptoms of Remission for the PANSS, *TiC-P* Trimbos/iMTA questionnaire for Costs associated with Psychiatric Illness - short version.

The Green Paranoid Thought Scales (GPTS) [81] is a self-report measure that assesses changes in paranoid experiences and in ideas of reference. It consists of 32 statements about experiences in the last month, sixteen items about ideas of persecution and sixteen items about ideas of reference. Items are scored on a Likert scale ranging from 1 (not at all) to 5 (totally). The range of the total score is 32 to 160, with higher scores indicating higher levels of paranoia. The GPTS has good internal consistency, is valid, reliable and sensitive to clinical change [81].

The Auditory Hallucination Rating Scale (AHRS), which is part of the Psychotic Symptom Rating Scale(PSYRATS) [82], is an eleven questions interview that assesses the severity of auditory hallucinations: their frequency, duration, location, loudness, causal attribution, negative content, the severity of negative content, the extent and the severity of discomfort and suffering, the disruption of daily life because of voice hearing and the experience of control over voices. Scores are on a range from 0 (for example,‘not’) to 5 (for example,‘continuously’). The range of the total score is 11 to 55. The inter-rater reliability is excellent (.79 to 1.00).

The Delusion Rating Scale (DRS) is part the Psychotic Symptom Rating Scale (PSYRATS) [82]. It assesses the severity of delusions. Six questions go into the extent and the duration of preoccupation with the delusion, the credibility, the extent and severity of discomfort and suffering, and the disruption of daily life because of the delusions. Items are scored from 0 (for example, ‘not’) to 5 (for example,‘continuously’). Total score ranges from 0 to 30. Inter-rater reliability is excellent (.79 to 1.00).

The ESM is an assessment technique designed to obtain repeated self-reports, using an electronic beeper that signals subjects to fill in a questionnaire at preselected but randomized time points for several days [83]. In T.TIP the effect of treatment on auditory (verbal) hallucinations is studied. Therefore, only participants that experience verbal hallucinations every day may participate. Participants who will be part of this ESM study carry a palmtop-like device called a Psymate[84], programmed to beep 10 times a day for six consecutive days at T0 and T6. The questionnaire consists of 50 self-exploratory questions used in previous studies, beginning with the most transient experiences (mood, thoughts and symptoms), followed by more stable items (context) and retrospective items in last position. All items are scored on Likert scales (range 1 to 7) or category boxes.

ESM has been proven to be a valid, reliable and feasible method of investigating psychotic experiences [35,85] by the use of face validity, comparison of aggregated data between groups, correlations between similar and dissimilar items and determining associations with available behavioral/external referents. ESM is useful for refining the phenomenology of psychotic symptoms, for investigating etiological mechanisms underlying psychosis and in clinical practice [86,87].

The Beck Depression Inventory second edition (BDI-II) [88] is a self-report that consists of twenty-one items. Each item is rated on a 4-point Likert-type scale ranging from 0 to 3, with higher scores indicating higher levels of depression. The measure asks respondents to rate statements characterizing how they have been feeling throughout the past two weeks. The maximum total score for all 21 items is 63. Score categories range from 0 to 13 (minimal depression), 14 to 19 (mild depression), 20 to 28 (moderate depression) and 29 to 63 (severe depression). Good psychometric properties have been shown for the original BDI [89] and for the 1996 revision BDI-II [88] that is adapted to depression criteria in the DSM-IV. The BDI-II shows good validity compared to the Hamilton Depression Rating Scale (Pearson *r* of 0.71). The test has high internal consistency (*α*=.91) [62].

The Personal and Social Performance Scale (PSP) [90] assesses social functioning as a secondary treatment outcome measure. The PSP scale is a clinician-rated scale that measures personal and social functioning in the domains of socially useful activities (for example, work and study), personal and social relationships, self-care, and disturbing and aggressive behaviors. Difficulty in each area is rated according to set criteria, using a six-point scale: absent, mild, manifest but not marked, marked, severe, and very severe. On the basis of the subscale ratings, a global score is rated by the interviewer, ranging from 1 to 100 in ten point intervals, where lower scores indicate lower functioning.

The PSP was shown to be able to detect changes in patients with both stable and acute psychotic disorders [91]. The PSP has been developed through focus groups and reliability studies on the basis of the social functioning component of the DSM-IV-TR Social and Occupational Functioning Assessment Scale (SOFAS). The PSP showed good (>0.80) interrater reliability and test–retest reliability [90-92].

The Posttraumatic Cognitions Inventory (PTCI) [93] assesses cognitions after having experienced a trauma. Note that the PTCI will be mentioned again in the section on ‘Tertiary measurements: predictors, moderators and mediators of treatment outcome’. The PTCI serves two goals: (a) post traumatic cognitions may be altered as a consequence of treatment; and (b) post traumatic cognitions may function as a predictor variable of treatment outcome. The PTCI consists of 33 items and three subscales. Negative Cognitions About Self (general negative view of self, permanent change, alienation, hopelessness, self-trust and negative interpretation of symptoms) contains 21 items). Seven items represent the second factor of Negative Cognitions About the World (unsafe world and mistrust of other people). Five items represent the third factor of Self-Blame. Participants rate each item on a 7-point Likert-type scale, from 1 (totally disagree) to 7 (totally agree). Thus, high scale scores indicate stronger maladaptive cognitions. The scores of the three factors are calculated by dividing the sum score by the number of items (factor scores range from 0 to 7). The total score is the sum of the three factor scores (maximum of 21). Internal consistencies of the three subscales were found to be excellent (0.86 to 0.97). The test-retest reliability was good (0.74 to 0.86). The PTCI was shown to discriminate better between individuals with and without PTSD (86% classified correctly) than other tools for assessing trauma-related cognitions [93]. Sensitivity and specificity were proven good [94].

The Structured Clinical Interview for Symptoms of Remission for the PANSS (SCI-SR, eight items) [95] is a brief eight-item interview that is used in research and treatment settings to assess remission of psychotic symptoms, based on eight items of the Positive And Negative Syndrome Scale (PANSS) [96]. In the present study it is part of the research of economic costs. The participant has to confirm functional status on four items: delusions, unusual content of thought, hallucinations and apathy. Scores on the other four items are based on observation and participants’ responses: conceptual disorganization, lack of spontaneity, blunted affect and posturing. Each item is rated using criteria described in the PANSS Manual. The PANSS determines severity of symptoms on 7-point Likert scales. Remission on the PANSS-SCI-SR is defined as a score of three (mild) or less for each item, maintained over a six-month period [97]. Compared to the total PANSS score the specificity of the remission criteria was 85%. The sensitivity was 75%. The remission criteria are both sensitive and specific indicators of clinical status. Additional analyses are required to determine if remission status predicts other outcomes, such as employment, independent living, and prognosis [98].

The Trimbos/iMTA questionnaire for Costs associated with Psychiatric Illness (TiC-P, short version) [99] will be used to assess the costs. Trimbos and the Institute for Medical Technology Assessment (MTA) developed this care consumption list. The TiC-P is commonly applied in the economic evaluation of treatment in mental health care, including trials on the cost utility of brief psychological treatment for anxiety (for example, see [98,100]. To be able to calculate the total direct medical costs, the first part of the Tic-P assesses the total number of medical contacts (outpatient visits, length of stay in hospital, use of medication, and so on). Afterwards, the data will be multiplied by unit costs of the corresponding health care services. Reference unit prices of health care services will be applied and adjusted to the year of this study according to the consumer price index. In the second part of the TiC-P a short form of the Health and Labor questionnaire (HLQ) [101] will be used to collect data on productivity losses. The Short-Form HLQ (SF-HLQ) consists of three modules that measure productivity losses: absence from work, reduced efficiency at work and difficulties with job performance.

The EuroQol (EQ-5D™) [102,103] is a standardized instrument for measuring health outcome. This patient-reported outcome measure has five dimensions: mobility, self-care, usual activities, pain/discomfort and anxiety/depression, and each dimension has three levels (no problem, some problem, severe problem). Together, these five dimensions make a simple descriptive profile that can be compared to a total of 243 health states scored using values obtained from a survey of the general population. Participants also point out a single index value for current health status on a scale from 0 (‘worst possible health’) to 100 (‘best possible health’). The EQ-5D measures and expresses quality of life in utilities. Utilities can be combined with cost-effectiveness data into Quality Adjusted Life Years (QALYs). The EQ-5D has good reliability and validity [103].

